## Abstract

**Background:**

The incidence of gallstones and gallbladder sludge is known to be higher in patients after gastrectomy than in general population. This higher incidence is probably related to surgical dissection of the vagus nerve branches and the anatomical gastrointestinal reconstruction. Therefore, some surgeons perform routine concomitant cholecystectomy during standard surgery for gastric malignancies. However, not all the patients who are diagnosed to have cholelithiasis after gastric cancer surgery will develop symptoms or require additional surgical treatments and a standard laparoscopic cholecystectomy is feasible even in those patients who underwent previous gastric surgery. At the present, no randomized study has been published and the decision of gallbladder management is left to each surgeon preference.

**Design:**

The study is a randomized controlled investigation. The study will be performed in the General and Oncologic Surgery, Department of Oncology – Azienda Ospedaliero-Universitaria Careggi – Florence – Italy, a large teaching institution, with the participation of all surgeons who accept to be involved in, together with other Italian Surgical Centers, on behalf of the GIRCG (Italian Research Group for Gastric Cancer).

The patients will be randomized into two groups: in the first group the patient will be submitted to prophylactic cholecystectomy during standard surgery for curable gastric cancer (subtotal or total gastrectomy), while in the second group he/she will be submitted to standard gastric surgery only.

**Trial Registration:**

ClinicalTrials.gov ID. NCT00757640

## Introduction

The incidence of gallstones and gallbladder sludge is known to be higher in patients after gastrectomy than in general population (15–25% versus 5%, 5 years after gastric surgery) [1-4]. This higher incidence is probably related to surgical dissection of the vagus nerve branches and the anatomical gastrointestinal reconstruction [5-7].

Moreover, the risk of developing gallstones may depend on the extent of gastrectomy (subtotal or total) and lymphadenectomy (D1 or D2) [4,8-10]. Concomitant cholecystectomy is not time consuming and substantially without additional risks for the patients, because complications during another abdominal procedure are known to be minimal [11-13]. In addition theoretic advantages will be represented by the avoidance of reintervention for cholelithiasis only.

However, not all the patients who are diagnosed to have cholelithiasis after gastric cancer surgery will develop symptoms or require additional surgical treatments [2-4] and a standard laparoscopic cholecystectomy is feasible even in those patients who underwent previous gastric surgery[14].

Due to the lack of specific data and to presence of contrasting studies, some Authors[4,8] recommend to perform a prophylactic cholecystectomy at the time of gastric surgery to avoid complications and impairment of quality of life in surviving patients, while others do not[1]. At the present, no randomized study has been published and the decision of gallbladder management is left to each surgeon preference.

## Methods

### Ethical Approval

The Cholegas Study was approved by the ethical Committee of the Careggi Hospital, Florence, Italy (and from all the local Committes of the participating centers).

### Design

The study is a controlled randomized trial. The study will be performed in the General and Oncologic Surgery, Department of Oncology – Azienda Ospedaliero-Universitaria Careggi – Florence – Italy, a large teaching institution, with the participation of all surgeons who accept to be involved in, together with other Italian Surgical Centers, on behalf of the GIRCG (Italian Research Group for Gastric Cancer).

The patients will be randomized into two groups: in the first group the patient will be submitted to prophylactic cholecystectomy during standard surgery for curable gastric cancer (subtotal or total gastrectomy), while in the second group he/she will be submitted to standard gastric surgery only.

### Randomization

The randomization will be obtained through a computer-generated program (GraphPad Software, Inc, La Jolla, California, USA). The randomization, will be done before the beginning of the study and it will consist with an ordered series of numbers with a corresponding letter: A for prophylactic cholecystectomy and B for gastrectomy only. This series of numbers will be kept in the Department of General and Oncologic Surgery in Florence and after gastric cancer diagnosis if the patient fulfills the inclusion criteria, either from Florence or from any other Center throughout Italy, and signs the consent a number, progressive as in order of inclusion, will be assigned to him or her. The letter corresponding to the number, and hence the type of procedure to perform, will be notify to the operating surgeon, who will proceed accordingly.

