### Inclusion and exclusion criteria

Inclusion criteria

• Patients suitable for curative surgery ≤ 80 years old

• Histhopatological confirmed gastric cancer (adenocarcinoma)

• Informed consent

Exclusion criteria

• Informed consent refusal

• Previous cholecystectomy

• Demonstrated cholelithiasis or biliary sludge

• Metastatic disease

• Metabolic diseases that may favour gallstones formation (hemolytic anemia, genetic hypercholesterolemia)

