### Data Collection

Patients' data files are generated containing demographic data and preoperative, operative, and postoperative information.

Pre-operative notes concern the history of gastric symptoms, the presence of associated diseases (cardiac, hypertension, diabetes, malignancy), duration of complaints (as an indication for the onset of the disease), and laboratory results of WBC count, serum bilirubin, gamma GT, and alkaline phosphatase. Ultrasound preoperative exclusion of gallbladder diseases is mandatory.

Operative data of concern are confirmation of a normal gallbladder, type of gastrectomy (subtotal or total), extent of lymphadenectomy (D1, D2 and 12^th ^node station, D3) and reconstruction. Postoperative notes of interest include the use of Total Parenteral Nutrition (TPN) or Enteral Nutrition (EN), complications, and length of hospital stay. Laboratory tests of WBC count, serum bilirubin, gamma GT, and alkaline phosphatase are also collected in postoperative days 3^rd ^and 7^th^.

Complications are classified as surgical infections (wound infection, subphrenic or subhepatic abscesses); noninfectious surgical problems (e.g. anastomotic leakage, bile duct injury, hemorrhage); remote infections (urinary or respiratory); and miscellaneous problems (e.g. pulmonary complications, deep venous thrombosis, cardiac complications, etc). The collected information are entered into a database as either continuous or categorical variables for statistical analysis.

A second surgeon (different from the one who participating in the intervention), aware of the operative findings but not the management of the gallbladder, will then assume the care of the patient. Postoperative care and ability to be discharged from the hospital will be determined by the second surgical team. This second surgical team will be blinded to the treatment of the gallbladder. The primary operative team will be in every moment available for emergent consultation.

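### The allocation list, letters included, is kept in the Florence surgical department that also recruits and operates, and the arm is fixed at consent, before operative confirmation of eligibility

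*Protocol article*

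**What the plan says.** The Randomization section describes a sequence generated by computer before the study starts: "it will consist with an ordered series of numbers with a corresponding letter: A for prophylactic cholecystectomy and B for gastrectomy only". On custody it says: "This series of numbers will be kept in the Department of General and Oncologic Surgery in Florence". The Design section names the same unit as a place where patients are treated: "The study will be performed in the General and Oncologic Surgery, Department of Oncology". Other Italian centres take part and draw on the same list, since patients may come "either from Florence or from any other Center throughout Italy".

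The number is given "after gastric cancer diagnosis if the patient fulfills the inclusion criteria" and once the patient "signs the consent a number, progressive as in order of inclusion, will be assigned to him or her". The matching letter then goes to the operating surgeon. No time relative to the operation is given.

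The entry criteria require a patient fit for surgery with curative aim. They exclude metastatic disease and "Demonstrated cholelithiasis or biliary sludge". The Data Collection section makes a preoperative ultrasound of the gallbladder compulsory and then lists what is recorded at surgery: "Operative data of concern are confirmation of a normal gallbladder". It also hands postoperative care and the discharge decision to a second team that does not know how the gallbladder was managed.

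**The concern.** Two features of the stated procedure weaken allocation concealment.

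The first is custody. A list that shows the letter against each number, used strictly in order and held in a department that recruits, lets a person with access know the arm of the next patient. That knowledge can affect whether a borderline patient is offered the trial, or when. Randomisation then no longer guarantees comparable groups among the Florence patients.

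The second is timing. The arm is fixed at consent, while some facts that bear on eligibility can still change at operation: resectability, unsuspected metastases and the state of the gallbladder. If the surgeon already knows the arm by then, the judgement on eligibility and the choice of operation are made with that knowledge.

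Both reach stated primary aims. Aim C compares complications, operative time and postoperative stay. Aim B concerns the incidence of gallstones. The Intervention section leaves the surgeon free on total or subtotal gastrectomy, D1 to D3 dissection, open or laparoscopic access, and reconstruction. The Introduction itself says that gallstone risk may depend on the extent of gastrectomy and of lymphadenectomy. A choice influenced by the arm could therefore distort operative time, complications and stone risk together.

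**Working it through.** The point rests on the stated procedure, so the check sets the sections side by side.

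1. **Can the next arm be read?** The Randomization section has the letter beside the number, the whole series made in advance, and numbers used in order of inclusion. Whoever sees the list and knows the last number used knows the next arm.
2. **Who is near the list?** It is kept in the Florence surgical department, which the Design section names as a study site. The article names no holder outside that department and no concealment step. It also does not say who inside the department may look.
3. **Does this apply to every centre?** No. Surgeons elsewhere do not hold the list, so for them it works as remote allocation.
4. **When is the arm fixed?** After diagnosis, inclusion criteria and consent. No operative finding is required first.
5. **What is still open then?** The criteria and the compulsory ultrasound are applied before surgery, so most ineligible patients should already be out. Ultrasound of the gallbladder does not settle resectability or metastases found only at operation, and a normal gallbladder is confirmed again at operation. Some late ineligibility remains possible.
6. **When does the surgeon learn the arm?** The article does not say. Disclosure before the operation is the natural reading, but it is an inference.
7. **What does the blinded second team cover?** Care after the operation and discharge. It has no bearing on enrolment or on decisions in theatre.

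**Sample size.** The plan's figure is 122 patients, 61 per arm. A log-rank calculation with exponential times reproduces it. The inputs are control hazard −ln(0.80)/5, loss hazard −ln(0.50)/5, uniform accrual over 2 years, minimum follow-up of 3 years, and 99.9% to 99.99% event-free in the cholecystectomy arm as a stand-in for 100%. The result is 60.7 to 61.5 per arm, or 122 to 124 in total. Loss in these inputs covers death and loss to follow-up. There is no separate allowance for patients found ineligible at operation. This figure neither supports nor refutes the point on allocation.

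**The case against.** The case on the other side has real force.

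- **Access is not stated.** The article says where the list is kept, not who may read it, and a condensed article may leave access control to the full protocol. This stands as a limit: foreknowledge is possible, not shown. The custody choice itself is stated, however, and it places the list with a team that has an interest in the allocation.
- **A reader might infer that eligibility is settled only at surgery.** The documents do not support that. The criteria apply before a number is given, ultrasound is compulsory, and the operative gallbladder check appears in a list of data to record, not as an entry gate. Only residual late findings are at issue.
- **A reader might infer that the plan excludes patients after randomisation.** No such rule is written. How such patients are analysed is commonly left to the statistical analysis plan.
- **A reader might infer that complications and stay are compared without any blinding.** The second team protects postoperative care and discharge. Operative time cannot be blinded, because the surgeon must know whether to remove the gallbladder. What can be protected is enrolment and the choices made before that step.
- **A reader might measure the harm as lost power.** Suppose 10% to 20% of patients dropped out of the analysis, a rate that the documents do not give. With expected control events of 61 × 0.1259 = 7.7, a planning formula, Φ(√events − 1.96), gives 79% at full size, 75% at 10% (6.9 events) and 70% at 20% (about 6.1 events). But simulating the log-rank test with no events in the cholecystectomy arm gives 94% at 61 per arm, 91% at 55 and 85% at 49. With 50% loss at 3 years instead, the simulated figures are 87%, 82% and 74%. These figures depend on an assumed rate, on the method and on an exclusion that the plan does not prescribe. They describe lost information, not bias, and are no evidence for this point.
- **Randomising before surgery is a legitimate design.** That is so. Allocation in theatre is an improvement here, not a correction of an invalid method.

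**Conclusion.** The point holds in a limited form. By the stated procedure, the next allocation is foreseeable at Florence to anyone in the department with access to the list. At every centre the arm is fixed before the operation has confirmed eligibility. The first part rests on the assumption that someone involved in recruiting or operating can see the list; the article neither says nor rules this out. The second part follows from the text, but its effect depends on when the surgeon is told the arm and on how often the operation overturns eligibility. The article gives neither.

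The size of any bias in aims B and C cannot be computed from the documents. The documents do not show that allocation was subverted, that the weakness extends to list custody at other centres, or that the trial loses a known amount of power. The point is a cheap and worthwhile improvement to a stated procedure, not a flaw that invalidates the design.

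**What to change.** - Have the list held by someone outside the recruiting and operating team, for example a trial or statistics office, or use sequential opaque sealed envelopes.
- Take consent before surgery as now, and register the patient irrevocably before any allocation is made.
- Assign and release the allocation in theatre, only after the surgeon has confirmed eligibility and recorded the planned gastrectomy, extent of dissection and approach.
- State in the Randomization section who holds the list and when the surgeon is told.

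The cost is a telephone call or an envelope in theatre, a change of list holder and slight scheduling inconvenience. No patients or procedures are added.

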### Intervention

Preoperative data collection will include patient demographics and comorbidities (genitourinary, cardiac, pulmonary, gastrointestinal, renal, or rheumatologic).

The standard surgery for gastric cancer includes both total and subtotal gastrectomy with lymphadenectomy (D1, D2, D3), either laparoscopic or laparotomic. All types of reconstructions are allowed, including either mechanic or hand-sewn anastomosis. The standard open or laparoscopic cholecystectomy includes Calot's dissection with the cystic duct and artery ligated prior removal. The fundus-first technique is also allowed. Drainage tubes are left on routine basis, and withdrawn according to surgeon's preference.

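### One national list, issued in order of inclusion, and unadjusted tests leave aim C open to chance imbalance by centre and procedure: a loss of precision, not a bias.

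*Protocol article*

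**What the plan says.** The Randomization section describes one list, made before the study starts: "it will consist with an ordered series of numbers with a corresponding letter: A for prophylactic cholecystectomy and B for gastrectomy only". On where it is held: "This series of numbers will be kept in the Department of General and Oncologic Surgery in Florence". Numbers go out consecutively across the country, to patients "either from Florence or from any other Center throughout Italy, and signs the consent a number, progressive as in order of inclusion". The operating surgeon then learns the result: "The letter corresponding to the number, and hence the type of procedure to perform, will be notify to the operating surgeon". No strata are mentioned, and a single series issued in national order of inclusion leaves no room for them.

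The population is broad. According to Intervention, "The standard surgery for gastric cancer includes both total and subtotal gastrectomy with lymphadenectomy (D1, D2, D3), either laparoscopic or laparotomic", and "All types of reconstructions are allowed, including either mechanic or hand-sewn anastomosis". The Design section has the Florence unit working "together with other Italian Surgical Centers, on behalf of the GIRCG", without giving the number or size of centres.

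Aim C, under Primary aims of the study, asks whether adding cholecystectomy raises the complication rate, operative time and postoperative stay. The Tests section gives chi-squared or Fisher tests for categorical variables and Mann-Whitney tests for continuous ones. Its only multivariable method, a Cox model, is attached to the onset of cholelithiasis.

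**The concern.** Operative time, complications and stay can be expected to vary with the extent of resection, the access route, the surgeon and local discharge practice. As written, neither the allocation nor the stated tests take account of centre or procedure for aim C. With only 61 patients per arm, one arm may by chance receive noticeably more total gastrectomies, and a small centre may contribute mostly to one arm. Variation between centres and procedures then stays in the error term, and the realised arm difference is harder to interpret. Aim C carries the safety case for the added procedure, so a blurred answer there matters. Allocation is already central, so some balance could be had cheaply.

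**Working it through.** **1. The plan's own figure.** Inputs from Power Calculations: 80% versus 100% free of cholelithiasis at 5 years, 2 years' accrual, 3 years' minimum follow-up, 50% survival at 5 years, 80% power, two-sided 5%.
- Event hazard in controls λ = −ln(0.8)/5 = 0.0446; loss hazard μ = −ln(0.5)/5 = 0.1386; sum L = 0.1833.
- P(event, control) = (λ/L) × [1 − (e^(−3L) − e^(−5L))/(2L)] = 0.2435 × [1 − (0.5771 − 0.4000)/0.3665] = 0.126.
- Freedman events as the hazard ratio tends to 0: (1.960 + 0.842)² = 7.85. N = 2 × 7.85/0.1259 = 124.7.
- The Lachin-Foulkes formula on the same inputs gives 121.3, so 122.

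The stated 122 is reproduced. This point does not touch the sample size.

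**2. Imbalance in procedure.** The share having total gastrectomy is not in the article; I assume 30% to 50%, that is K = 37 to 61 of 122. With a 61:61 split, the number X in one arm is hypergeometric (122, K, 61) and the between-arm difference in shares is (2X − K)/61.

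| Assumed share | K | SD of difference | P(≥10 points) | P(≥15 points) |
|---|---|---|---|---|
| 30% | 37 | 8.4 points | 24% | 5% |
| 40% | 49 | 8.9 points | 27% | 6% |
| 50% | 61 | 9.1 points | 28% | 7% |

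**3. Imbalance by centre.** For a single centre of assumed size m, the number in one arm is hypergeometric (122, 61, m):
- m = 12: 9:3 or worse, 12.6%
- m = 10: 7:3 or worse, 32%
- m = 6: 5:1 or worse, 21%
- m = 4: all in one arm, 12%

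The chance that at least one centre splits 75:25 or worse depends on the layout, which is not given (simulated):

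| Assumed layout | Probability |
|---|---|
| Ten centres of 12 to 13 | 69% |
| Florence 62, five centres of 12 | 48% |
| Florence 62, three centres of 20 | 7% to 8% |
| Four centres of about 30 | 0.4% |

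**4. Effect on complications.** Assume complication risk differs by 10 to 20 points between procedures. A 15-point imbalance then shifts the arm difference by 0.15 × 10 = 1.5 to 0.15 × 20 = 3 points. The standard error of the arm difference is √(2p(1−p)/61): 7.2 points at p = 0.20 and 8.3 points at p = 0.30 (assumed rates). The article has no figures from which to do the same for operative time and stay.

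**5. Validity.** I simulated 40,000 trials with ten unequal centres (5 to 40 patients), centre complication rates from 10% to 45%, a further 15 points for total gastrectomy in 40% of patients, and no treatment effect. The unadjusted test rejected in 4.9% of trials, and the mean arm difference was 0.06 percentage points, which is zero within simulation error.

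**The case against.** The strongest reply is that nothing here is an error: central, unstratified 1:1 randomisation is a valid design. That stands, and step 5 confirms it. A reader might infer that the aim C comparison is biased or its type I error inflated. The documents do not support that, because imbalance from a random list falls in either direction and averages to nothing.

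Other parts of the objection also stand:
- The 69% rests on ten equal centres. Design describes Florence as a large teaching institution, and layouts with few or large centres bring the figure below 10%. One uneven small centre also involves only a small part of the sample.
- The shift in complications is small beside its standard error.
- The Introduction's remark that "the risk of developing gallstones may depend on the extent of gastrectomy (subtotal or total) and lymphadenectomy (D1 or D2" concerns stones. It does not show that aim C outcomes depend on extent; that premise is clinical plausibility. For stones, the plan assumes none in the cholecystectomy arm and already has a Cox model.
- Data Collection has discharge decided by a second team blinded to gallbladder management, so differences in discharge practice between centres are not tied to arm.
- Extent of gastrectomy, lymphadenectomy and reconstruction are recorded, so an analysis plan not shown could adjust for them.

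What does not stand is that the point merely notes missing detail. The article states the allocation mechanism, and no analysis plan can change how patients were allocated. Adjustment recovers part of the precision, but a small centre that falls wholly in one arm still offers no within-centre comparison.

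**Conclusion.** The point holds as a matter of efficiency and chance balance, and its weight is moderate to low. One national series combined with unadjusted tests leaves about a one-in-four chance of a 10-point imbalance in extent of gastrectomy, if 30% to 50% of patients have the total operation. The risk of a badly split centre is anywhere from under 1% to about 69%, depending on a layout the article does not give. The calculations take the 61:61 split from Power Calculations; Randomization itself does not say how the list is balanced.

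A reader might also infer that the list should be stratified fully by centre and procedure. The figures argue against it: ten centres by two procedures is 20 strata, or 122/20 ≈ 6 patients each. Many blocks would stay incomplete, and because the surgeon is told each allocation, the next one would be easier to guess.

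**What to change.** **Allocation.** Keep the central list in Florence but stratify it coarsely: Florence versus other centres, or large centres separately with small ones grouped. Add planned total versus subtotal gastrectomy only where strata stay large enough. Record the planned extent before the allocation is released, since the surgeon is told the arm and the final extent may be settled at operation. Use random permuted blocks of varying, undisclosed size.

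**Analysis.** Analyse aim C outcomes stratified by, or adjusted for, centre group and planned extent. Examples are a stratified rank test or a linear model for operative time and stay, and Mantel-Haenszel or logistic regression for complications. If recruitment has begun and the list cannot be changed, this part alone is still worth having.

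**Cost.** A few more lists before the start, one more field at enrolment, and slightly greater predictability of allocation, which coarse strata and varying blocks limit. The sample size stays at 122.
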